### Procedure

2.3

All participants were measured twice with an interval of five weeks (± one week), since a marked improvement is expected in the first six weeks of a LBP episode [25]. During this five-week interval, the participants with LBP received usual care in a primary care physiotherapy clinic. The therapists of these clinics received information about possible exercises for motor control and sensory accuracy, but were free in their choice of therapy form, duration, and intensity. However, during therapy they were not allowed to use the tests of which the results served as outcomes in the present study. All participants first underwent a T1 weighted MRI of the brain, after which they completed self-reported questionnaires, performed quantitative sensory tests, a motor control test, sensory tests and underwent TMS to determine the organization of M1. The MRI was only conducted before the first measurement. Below, each of these assessments is described in detail. See Fig. 1 for a flowchart of the study.

**Fig. 1 fig1:**
[figure not shown]
Flowchart of the study. MRI, Magnetic Resonance Imaging; TMS; Transcranial Magnetic Stimulation; LBP, Low Back Pain; NPRS, Numeric Pain Rating Scale; ODI, Oswestry Disability Index; PASS, Pain Anxiety Symptom Scale; CSI, Central Sensitization Inventory; PPT, Pressure Pain Threshold; CPM, Conditioned Pain Modulation.

### Assessments

2.4

#### Questionnaires

2.4.1

All participants completed a questionnaire regarding demographic variables. Participants with LBP also completed 1) a general questionnaire containing questions on location and duration of their pain; 2) a Numeric Pain Rating Scale (0–10); 3) the Oswestry Disability Index; 4) the Pain Anxiety Symptom Scale; and 5) the Central Sensitization Inventory. All questionnaires have adequate reliability and validity [[26], [27], [28], [29], [30]]. At 5-week follow-up, participants with LBP indicated their overall level of recovery on a Global Perceived Effect scale (GPE-Dutch Version, 7-point Likert scale) and completed the Numeric Pain Rating Scale, Oswestry Disability Index, Pain Anxiety Symptom Scale and Central Sensitization Inventory. Participants without LBP reported whether they were still free of LBP.

For our analyses, we are interested in those participants with LBP who showed recovery, versus those who did not. These groups (recovered and non-recovered LBP participants) are defined based on their ‘Global Perceived Effect’ after 5 weeks. The LBP participants is asked how much their back condition has improved or deteriorated on a 7-point Likert scale. Category 1 (‘completely recovered’) and category 2 (‘much improved’) will be considered as recovered. Category 3 (‘slightly improved’), 4 (‘equal’) and 5 (‘slightly deteriorated’) will be considered as ‘unchanged’, category 6 (‘much deteriorated’) and 7 (‘completely deteriorated’) as deteriorated. Therefore, category 3 till 7 will be considered as non-recovered [31].

#### Quantitative sensory testing

2.4.2

Vibration sense, pressure pain threshold (PPT), conditioned pain modulation (CPM) and temporal summation of pain were performed according to the recommended protocols [32,33]. For these tests, the participant was positioned prone, and familiarization was performed on the right hand.1)Vibration sense

A Rydel-Seiffer tuning fork (64 Hz, 8/8 scale; US Neurologicals, WA) was percussed and then placed over the spinous process of L4. When the participant indicated that vibration could no longer be felt, the corresponding value was determined from the scale on the prongs of the fork, ranging from 0 to 8 (with higher scores better vibration sense). The mean of three consecutive trials is used to determine the vibration threshold [[32], [33], [34]].2)Temporal summation of pain

First, a single pinprick (256 mN, MRC-systems GmbH, Heidelberg, Germany) was applied on the skin, 3 cm lateral to the spinous process of L5 on the (most) painful side. After 10 s, a train of 10 stimuli was applied at 1 Hz within an area of 1 cm^2^. This was repeated five times, with a 1-min rest between repetitions. Temporal summation was calculated by subtracting the mean Numeric Pain Rating Scale of the single stimuli from the Numeric Pain Rating Scale of the trains of 10 stimuli.3)Pressure Pain Threshold

A digital algometer (Wagner Instruments Model FDX-25, Greenwich, USA) was placed perpendicular to the skin, 3 cm lateral to the L5 spinous process on the (most) painful side, as outlined for the temporal summation. In case of equal intensity of LBP on both sides, the side of the measurement was randomized. The pressure was increased at a rate of ∼5 N/s. The participant was asked to indicate when the sensation of pressure changes to a sensation of painful pressure. The threshold is based on the mean of three repetitions.4)Conditioned Pain Modulation

After three baseline PPT measures, the participant submerged the right hand in a portable insulated 10 L container (Curver, the Netherlands), filled with water cooled to 10° Celsius, as measured with a digital thermometer). As soon as the pain intensity for the hand in the water reached 4/10, three PPT measures were performed at the same location as the baseline PPT measures, with 30s rest periods between PPTs. Numeric Pain Rating Scale scores for hand pain were recorded following each PPT. The relative and absolute CPM effect will be calculated as recommended [35]. The relative CPM effect will be calculated by subtracting the PPT value obtained during the cold pressor test from the baseline PPT; then the resultant value is divided by the baseline PPT. The value is then multiplied by 100 to obtain percentages. The absolute CPM effect will be calculated by subtracting the mean of the three PTT measures during the conditioning stimulus from the baseline PPTs [36]. In this way, pain inhibition will be reported by a negative value and pain facilitation by a positive value [35].

#### Motor control

2.4.3

Motor control was assessed with a spiral tracking test based on a previous study [4]. A custom-built sensor was attached to the skin at the level of the spinous process of T12. The sensor consists of an inertial measurement unit (MPU9250) and a microcontroller that processes the measurements with a sample rate of 100 Hz (SAMD21G18A). The orientation of the movement sensor was visualized by a green pointer on a computer monitor, placed in front of the participant. The participant was sitting in a relaxed upright position (i.e., not slumped, not in lordosis). The monitor also showed a red pointer (target) and a spiral. The red pointer started moving anticlockwise along the lines of the spiral figure, from the center to the periphery. The task for the participant was to follow the red pointer as precise as possible by moving the green pointer with the torso. The test ended automatically when the red pointer reached the end of the spiral. The test took about 2 min to complete.

The tracking error will be calculated based on the absolute difference between the target angle and the actual inclination angle of the trunk in the sagittal (x) and transversal (y) axis of motion [4]. In a separate reliability study, we will determine the variables that are most suitable for further analysis. Potential outcome variables will be selected from three categories: 1) degrees (the mean of a subset of the tracking errors, ranging from the closest 10% to the closest 90% errors; 2) time (the mean of a subset of the tracking errors, expressed in the time spent in an area smaller than X° of error) and 3) path (the sum of all errors, in degrees over one trial). More information about the measurement instrument and procedure is provided in Appendix A. Data from the sensors will be analyzed using custom-written Matlab scripts (R2014B, The MathWorks, Natick, MA).

#### Sensory tests

2.4.4

1)Graphaesthesia test

After a video instruction for the participant about the test procedures, a cross was drawn on the lower back, creating four quadrants of ∼5 × 5centimeters, with L3 at the center of the cross. Five numbers were drawn per quadrant (in total 20) with the back of the holder of a monofilament [37]. The participant had to recognize the number within 3 s. Numbers between zero to nine were used, apart from one and five as those are too easy to identify. The numbers were randomized per quadrant. Familiarization was performed by drawing one random number in each quadrant. The participant received no feedback on whether the number was correctly indicated during the familiarization and test. At the five-week follow-up, the same numbers were used in the same quadrant as at baseline, but in a different order. The error rate will be calculated by dividing the number of incorrect answers by 20.2)Two-point discrimination threshold

After a video instruction for the participant about the test procedures, two-point discrimination threshold testing was performed at 2 cm left and right from the spinous process of L1, L3 and L5 (six locations) using a 2-point discriminator (Carolina Biological Supply Company, Burlington, NC, USA). The calipers rest for 1 s perpendicular on the skin with a pressure corresponding to first blanching of the skin [38]. The test started with the calipers at 20 mm distance which was increased in five mm steps as long as the participant identified only one stimulus. When the participant identified two stimuli, the caliper was applied again with another 5 mm step increase. If the participant again identified two points, the distance when two stimuli were identified first is considered as the 2-point discrimination threshold [38]. The sequence of the location was randomized per measurement session. The same sequence was used for every participant. To keep the participant unaware of the increase in distance between the two points of stimulation, once per five stimuli only one point or two points with the biggest distance of the 2-point discriminator were stimulated [38]. These ‘in between’ stimulations were not used for data analysis. Familiarization was performed by placing the calipers once over three locations (L1, L3 and L5) left or right). The locations and distances of the calipers for familiarization were randomized. The participant received no feedback on the correctness of feeling one or two points during the familiarization and test.

#### Reorganization of M1

2.4.5

For more precise navigation of TMS, and to enable analysis of the same positions over time [39], we performed T1 weighted MRI scans for each participant (SIEMENS MAGNETOM Vida-XQ-32 Numaris/X VA20A-04 ML; matrix size 263mmx 350 mm x 350 mm, Voxel Size 1.0 × 1.0 × 1.0 mm³, TR/TE 2400/2.26 ms). Whole-brain grey matter was segmented using SPM12 software [40] for use in neural navigation (Neural Navigator 3.4, BrainScience Tools, The Netherlands).

Surface electromyography (EMG) was used bilaterally to record muscle activity of the longissimus muscle at the level of L3 and L5, and of the internal and external abdominal oblique muscles. Disposable, bipolar pre-gelled rectangular surface ECG electrodes (Ambu Blue Sensor N, Medicotest, Ølstykke, Denmark: AG/AgCl) were used. These electrodes were placed pairwise according to the SENIAM recommendations [41], after cleaning the skin with alcohol. The ground electrode was attached to the skin at the level of the spinous process C7. EMG was captured during the full TMS stimulation protocol at a rate of 2 kHz using a 16-channel Porti EMG device (Twente Medical Systems International B.V., Enschede, The Netherlands).

Prior to the TMS measurements, the MVC was determined. The participant was asked to perform a maximal contraction against resistance in sitting for 5 s and to do so three times [11]. To lower the threshold at which a Motor Evoked Potential (MEP) could be evoked, pre-activation at 20% of the Maximum Voluntary Contraction (MVC) of the longissimus muscle was asked during the TMS measurements. The pre-activation percentage of 20% was based on previous research [10,12,16,17,42], and did not cause subjective signs of fatigue in any of the participants.

This activation was obtained by having the participant sitting with a straight back, and when required resist a weight attached via a pully system to a custom made velcro harness which pulls the participant forward. On a computer screen a feedback line was provided based on the % of MVC the participant was using. A small deviation of the feedback line was allowed [12]. The tester gave verbal instructions when the deviation of the feedback line was too large, e.g. when the participant sat in a slumped position.

A Magstim 200^2^ stimulator (Magstim Company Ltd., Whitland, Dyfed, UK) was used to deliver a single-pulse TMS. The hemisphere contralateral to the side of the highest pain intensity was stimulated, using a figure-of-eight coil with 70 mm windings. The coil was orientated 45° to the sagittal plane, tangential to the scalp to induce currents in the cortex along the posterior to anterior direction [43]. Neural navigation software stored the position and orientation of the coil with respect to the head for each stimulation. The stimulation intensity was set at 100% output of the stimulator, as 120% of the motor threshold of the longissimus muscle generally exceeded the maximum output of the stimulator for most participants [9,10]. The hemispheres in the participants without LBP were measured corresponding to the hemispheres measured in the LBP participants.

During the TMS protocol, the EMG activity of the longissimus muscle at the level L3 of the painful site was monitored for the presence of MEPs. We used a protocol with 100 stimulations at pseudorandom positions using an interstimulus interval of approximately 4 s [42,44], covering the area of the motor cortex using a predefined 7 × 7cm grid, starting at the midline of the vertex. When we also found MEPs at the borders of the grid, stimulations were given in the surroundings, to make sure the area that can be stimulated was completely covered. The measurements were conducted according to the TMS checklist for methodological quality [45]. The MEPs of the other muscles were also recorded, but these were not monitored online. These data will also be reported and analyzed.

The data of the neural navigation, combined with the EMG will be analyzed in Matlab (R2019b) in accordance with Jin et al., 2022 [43]. The EMG data will be high pass filtered at 30 Hz. First, to correct for differences in the shape and the size of an individual's brain, registration to Montreal Neurological Institute space will take place [46]. Then the MEPs will be defined as 500 ms episodes following a stimulation in which the peak-to-peak amplitude is higher than 20 × σ. MEPs with peak-to-peak amplitude higher than 1 mV will be removed as these are likely artefacts. We will visually inspect all identified MEPs. Then, we will calculate for each muscle (longissimus muscle level L3 and L5, internal and external abdominal oblique muscles a) the CoG [10] and b) the cortical area from which stimulations can be elicited, by means of our custom algorithm (see Jin et al., 2022 [43] and https://github.com/marlow17/surfaceanalysis), see Appendix B).

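### The printed MEP rule searches the full 500 ms after each pulse with no latency limit, so unrelated transients between 20σ and 1 mV can be flagged as MEPs or set the CoG weight

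*Protocol article*

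**What the plan says.** All the processing rules are in section 2.4.5 (Reorganization of M1) of the protocol article, in this order:

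- Recording: "EMG was captured during the full TMS stimulation protocol at a rate of 2 kHz".
- Filter: "The EMG data will be high pass filtered at 30 Hz".
- Detection: "Then the MEPs will be defined as 500 ms episodes following a stimulation", namely those "in which the peak-to-peak amplitude is higher than 20 × σ". The text gives no start offset, no latency limit and no definition of σ.
- Ceiling: "MEPs with peak-to-peak amplitude higher than 1 mV will be removed as these are likely artefacts".
- Manual step: "We will visually inspect all identified MEPs". No rejection criteria and no masking are stated.
- CoG and area are then calculated for each muscle: longissimus at L3 and L5, and the internal and external obliques.

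The section also says that the data, "combined with the EMG will be analyzed in Matlab (R2019b) in accordance with" a cited methods paper, feed a custom algorithm described in a public code repository and Appendix B.

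Three other statements matter. The Introduction defines the CoG as an amplitude-weighted centre. The Discussion says that the area calculation leaves out stimulations that produced no MEP. The Discussion also plans an exploratory silent-period subanalysis.

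**The concern.** An MEP is a response time-locked to the pulse. In a trunk muscle it is expected early in the window (general physiology, not stated in the article). The printed rule does not use that timing: a transient 400 ms after the pulse qualifies as readily as one in the first tens of milliseconds.

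This matters in two ways. First, a flagged transient at a site with no true response adds that site to the area and to the CoG. Second, at a site with a true response, a larger deflection elsewhere in the window supplies the peak-to-peak amplitude, and so the weight. Longissimus CoG is the outcome on which the sample size rests, and CoG and area are the M1 outcomes throughout section 2.6.

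Exposure probably differs by muscle. The article specifies "pre-activation at 20% of the Maximum Voluntary Contraction (MVC) of the longissimus muscle was asked during the TMS measurements", and only longissimus at L3 was watched online. If σ is the SD of background EMG, a muscle with little background activity has a low threshold, and the obliques were neither deliberately pre-activated nor monitored.

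**Working it through.** The article gives no false-detection figure to reproduce, and its sample size is not in question here. The checks below ask what the printed rule lets through.

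**1. Does steady background pass 20σ?** Samples per window = 0.5 s × 2,000 per s = 1,000. For independent Gaussian noise, 20,000 simulated windows of 1,000 samples gave a mean peak-to-peak of 6.48σ, a 99.9th percentile of 8.38σ and a maximum of 9.63σ. The threshold is 20 / 6.48 = 3.1 times the usual background value. If σ is the SD of that background, steady noise does not pass and only transients do.

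**2. Which transients are accepted?** The accepted range runs from 20σ to 1 mV (1,000 µV). The σ values are assumptions.

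| σ (µV) | Accepted peak-to-peak (µV) |
|---|---|
| 3 | 60 to 1,000 |
| 5 | 100 to 1,000 |
| 20 | 400 to 1,000 |
| 50 | none (20 × 50 = 1,000) |

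The ceiling closes the range only when σ reaches 50 µV. With low background the range is wide.

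**3. How often does a heartbeat fall in the window?** Pulses are about 4 s apart and taken as unrelated to the cardiac cycle. For window length w in seconds and heart rate HR, the probability is w × HR / 60. Heart rates and the 50 ms comparison window are assumptions.

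| HR (beats/min) | w = 0.5 s | w = 0.05 s |
|---|---|---|
| 50 | 42% | 4.2% |
| 60 | 50% | 5.0% |
| 70 | 58% | 5.8% |
| 80 | 67% | 6.7% |
| 100 | 83% | 8.3% |

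The exposure ratio is 0.5 / 0.05 = 10 at every heart rate. In the 100-pulse protocol, 60 to 80 beats/min means 50 to 67 windows with a heartbeat, against 5 to 7.

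**4. From exposure to false MEPs.** A heartbeat becomes a false MEP only if its filtered amplitude in that channel lies between 20σ and 1 mV and it survives inspection. The article gives neither σ nor the filtered amplitude, so this rate cannot be computed.

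**5. Direction of the effect.** Suppose a share f of the total CoG weight comes from false detections unrelated to coil position, with mean location C. Then observed CoG = (1 − f) × true CoG + f × C. With the same f and C in two groups, the observed group difference is (1 − f) × the true difference. That is dilution, and random variation in f adds noise. For area, false sites away from the true representation enlarge the estimate.

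**The case against.** The strongest case on the other side has four parts.

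*Other safeguards exist.* The signal is high-pass filtered, events above 1 mV are dropped, and every identified MEP is inspected before CoG and area are calculated. An ill-timed heartbeat is the kind of event an inspector could catch. This stands. A reader might infer that any deflection counts, or that the endpoints are contaminated. The text supports neither, only that contamination is possible.

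*Details may be elsewhere.* The methods paper, repository and Appendix B may set a latency window, blank the pulse artefact and define σ. This stands in part. It is why the pulse artefact is not charged here: it follows every pulse, so without some handling it would flag or discard nearly every stimulation, yet the Discussion describes stimulations without an MEP. It does not rescue the 500 ms definition, which is printed as the rule. If a narrower window is used, the article misdescribes it.

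*Masking.* A reader might infer that the inspection is unmasked. The article is silent, and a condensed article often leaves this to the full protocol. Silence is not evidence of unmasked review. Nor do the documents tie heartbeats or bursts to group, visit or recovery, so a biased group difference is not shown.

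*The σ values are assumed.* The obliques are not described as relaxed: participants sat upright and some resisted a forward pull. Longissimus at 20% MVC would have a higher σ if σ reflects background EMG. This stands, so the ranking of muscles by risk is only probable.

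**Conclusion.** The point holds as a weakness in a stated rule, worth correcting before the analysis is run. As printed, a transient at any time in the 500 ms with amplitude between 20σ and 1 mV can be flagged as an MEP or set the CoG weight, and only an inspection without stated criteria or masking can remove it.

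The size that can be given is exposure: 50 to 67% of 500 ms windows contain a heartbeat at an assumed 60 to 80 beats/min, against 5 to 7% of 50 ms windows. It would be wrong to read 50 to 67% as a false-MEP rate, for the reason in step 4. The expected consequence is mainly noise and dilution in area and CoG, probably greatest in muscles with low background EMG that were not monitored online. It rests on three assumptions: trunk EMG carries some heartbeat signal that survives a 30 Hz high-pass filter, σ is a background SD, and the written rule is the one applied.

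**What to change.** In section 2.4.5:

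1. Detect and measure the MEP only in a short latency window that starts after the pulse artefact. Set its limits on data pooled over all participants and visits, blind to group, visit and recovery.
2. Define σ (epoch and channel), and apply the 20σ and 1 mV limits inside that window.
3. Keep the 500 ms segment for the silent-period subanalysis only.
4. State the rejection criteria for the visual inspection, carry it out on files coded to hide group, visit and recovery, and report rejections by group and visit.
5. If the cited methods paper or Appendix B already sets such a window, correct the printed definition to match.

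The cost is a script edit, coded file names and a few sentences. No new data or staff are needed, since the article describes this analysis as still to be done. The downside is that an unusually late true response could be missed; the pooled latency check would show whether such responses occur.

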### Sample size estimation

2.5

The sample size was calculated based on a cross-sectional comparison between two groups, using a continuous outcome, with a power of 0.80 and an α of 0.05. We used the mean and pooled standard deviation (0.68) regarding the CoG of the longissimus muscle from previous similar research, investigating the differences in CoG between the groups participants with LBP (n = 27; mean (SD): 1.4 (0.61)) and participants without LBP (n = 23; mean (SD:) 0.8 (0.77)) [9]. The calculation produced a required sample size of N = 21 per group. Taking a 15–20% drop out risk into account, the required sample size per group was 25.

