## Discussion

3

This study will provide evidence about 1) differences in the organization of M1 of trunk muscles between people with and without LBP, and whether the organization of M1 relates to motor control and sensory impairments (cross-sectional component) and 2) reorganization of M1 over time and its relation with changes in motor control and sensory impairments and experienced recovery (longitudinal component).

In this study we applied the following procedures to facilitate a precise navigation and calculation of the organization of M1: 1) we used individual whole-brain anatomical MRI's for the navigation of TMS. This makes it possible to adjust for differences in the shape and the size of the participants' brain and to enable analysis of the same absolute positions over time; 2) in the data-analysis, a custom-made and novel 3D analysis method will be used to calculate the representations of muscles on M1. This method allows calculating the cortical area from which a muscle can be excited, while explicitly excluding stimulations where no MEP was found, and without making assumption about the underlying geometry; 3) since we use a pseudo-random stimulation protocol, our stimulations are closer together than grid-based protocol studies, thus allowing for greater spatial resolution of our outcome measures [44].

The representation of several trunk muscles on M1 will be calculated, and subsequently a possible overlap of these muscles can be demonstrated. This could provide us with more insight into the theory of loss of differential activation of trunk muscles in LBP [10]. Because we have multiple outcomes and variables in this study, we find it appropriate to carry out a multivariate multilevel analysis, where we can correct for multiple testing and dependency of observations.

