This study has some limitations. We defined the selection criteria in such a way that we anticipated a proportion of the participants to recover after five weeks. We therefore did not want to solely recruit people with persistent pain, but opted to include people with a fluctuating pain trajectory. However, it is possible that either the number of recovered or the number of non-recovered LBP participants will be small. This may influence the power of the statistical analysis. However, in general the power of longitudinal analyses is higher than the power of cross-sectional analyses, because of the gain in the number of observations. Despite some loss because of the partly correlated observations, more observations will remain for the analysis than in a cross-sectional design. Based on the sample size calculation, for the comparison between participants with LBP and participants without LBP of cortical reorganization over time, the power is therefore expected to be sufficient.

Although people with longer lasting symptoms might be more prone to reorganization of M1, we decided to include participants with a pain duration >24 h [20] who were seeking medical or physiotherapy care, since a marked improvement is expected in the first six weeks of a LBP episode [25].

In this study we used 100% of the maximum stimulator output, as 120% of the motor threshold of the longissimus muscle generally exceeds the maximum output of the stimulator [9,10]. Therefore, no individual stimulation intensity was used. Subsequently, for some participants the stimulation intensity could be too high for accurate determination of the area [43] and for others too low for inducing MEPs.

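### The stated 80% power covers one unadjusted longissimus CoG comparison, while the plan analyses CoG and area in four muscles, reserves none as primary and says it corrects for multiple testing

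*Protocol article*

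**What the plan says.** Section 2.5 bases the sample size on one baseline contrast of the two groups, "using a continuous outcome, with a power of 0.80 and an α of 0.05". The outcome is the longissimus CoG from an earlier study: "participants with LBP (n = 27; mean (SD): 1.4 (0.61") against "participants without LBP (n = 23; mean (SD:) 0.8 (0.77"), with a pooled SD of 0.68. The result is 21 per group, raised to 25 for dropout. Section 2.5 mentions neither multiplicity nor the other muscles.

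The planned outcomes are wider. Section 2.4.5 states "we will calculate for each muscle (longissimus muscle level L3 and L5, internal and external abdominal oblique muscles a) the CoG [10"), followed by the cortical area. Section 2.6 puts the muscles together in multivariate mixed models. The Discussion confirms CoG and area as the two measures. No muscle, measure or contrast is named as primary.

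The Discussion gives the number of outcomes and variables as the reason for the method: "we find it appropriate to carry out a multivariate multilevel analysis, where we can correct for multiple testing and dependency of observations". In the limitations it refers back to the sample size calculation and says of the comparison of cortical reorganization over time between people with and without low back pain that "the power is therefore expected to be sufficient".

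**The concern.** A power figure belongs to a decision rule. The figure in 2.5 belongs to one test with the whole 0.05 spent on it. The Discussion describes an analysis of several outcomes in which multiple testing is corrected. If that correction covers the longissimus CoG comparison, the 80% was not derived for the rule that will be used.

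At stake is how a null result is read. Someone who sees a corrected, non-significant longissimus CoG difference would take it to come from a study with 80% power for the difference it was sized on. The same calculation is also cited in support of adequate power for a different, longitudinal comparison.

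**Working it through.** **Inputs from section 2.5.** Difference 1.4 − 0.8 = 0.6; SD 0.68; standardized effect d = 0.6/0.68 = 0.882; power 0.80; α 0.05; equal groups. Sidedness is not stated. Two-sided is inferred because a one-sided test gives 16 per group, not 21.

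**Step 1: reproduce the plan's figure.** n per group = 2(z₀.₉₇₅ + z₀.₈₀)² / d² = 2(1.960 + 0.842)² / 0.882² ≈ 20.16 with unrounded quantiles, rounded up to 21. The printed N is reproduced for one test at an unadjusted two-sided 0.05. Noncentral-t power at 21 per group is 79.7% (normal approximation 81.6%). The quoted SDs pool to √[(26 × 0.61² + 22 × 0.77²)/48] = 0.688, which still gives 21 by this formula.

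**Step 2: count the planned outcomes.** Four muscles (longissimus L3, longissimus L5, internal oblique, external oblique) × two measures (CoG, area) = 8. CoG alone gives 4. This counts each CoG as one number and leaves out the longitudinal and association analyses.

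**Step 3: power for the sized difference if α is split equally.** The Bonferroni split is an assumption; the article names no procedure. Two-sided t-test, noncentrality d√(n/2), 2n − 2 degrees of freedom, α = 0.05/k:

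| Analysable per group | k = 1 | k = 2 | k = 4 | k = 8 |
|---|---|---|---|---|
| 20 (25 less 20%) | 77.6% | 67.6% | 57.1% | 46.8% |
| 21 | 79.7% | 70.1% | 59.9% | 49.7% |
| 25 (no loss) | 86.4% | 78.7% | 69.9% | 60.4% |

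The normal approximation is 4 to 5 points higher at 21 per group (64.1% for k = 4, 55.0% for k = 8). For 80% power by t-test, 31 analysable per group are needed for k = 4 and 35 for k = 8.

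**Step 4: a less strict correction.** Holm over the four CoG tests at 21 per group was simulated with 20,000 replicates and assumed common correlations of 0.3 to 0.8. Power for one longissimus CoG test is about 62% if only the two longissimus sites shift by 0.6, and about 68–70% if all four muscles do.

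**Step 5: one joint test at 0.05.** This uses a Hotelling approximation with eight outcomes, 21 per group and an assumed common correlation of 0 to 0.7. Power runs from 39% to 90% if one outcome differs by 0.882 SD, and from 53% to almost 100% if all eight do. The document gives neither the correlations nor the other effects, so no single figure follows.

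**The case against.** The strongest reply is that nothing in 2.5 is miscalculated. The section says openly that it rests on one continuous outcome and does not claim 80% for eight. That stands: the arithmetic is right.

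Next, the Discussion places the correction inside the multivariate model and says only that it can be made. No divided α appears anywhere. A reader might infer that the plan leaves the study with 50–60% power. The document does not support that: the range needs Bonferroni over four to eight tests at 21 per group. Holm gives more, 25 analysable per group gives more, and a joint test could give less or more than 80%.

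The sized contrast is also a baseline one, so loss to the five-week follow-up need not remove data from it. If all 25 per group are analysable, unadjusted power is 86.4%. Some loss at baseline remains possible, because the Discussion accepts that the stimulation may be too weak to induce responses in some participants.

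An article may also leave the procedure and the test family to an analysis plan, so their absence is not the point here. What remains is a mismatch between two things the article does state: a power figure for one unadjusted test, and an analysis of several outcomes justified by correction for multiplicity. Holding the sized comparison outside the correction would reconcile them, but nothing in the article does so. Online monitoring of the L3 longissimus during stimulation (2.4.5) is a measurement choice and reserves no α. Nor does 2.5 say that its CoG value was taken at L3.

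Finally, the longitudinal claim leans mainly on the gain from repeated observations, and the same paragraph warns that the recovered or non-recovered group may be small. A reader might infer that the longitudinal comparison is underpowered. The baseline figures above do not show that. They show only that the cited calculation does not address it.

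**Conclusion.** The point holds in conditional form. The 80% applies to one baseline comparison of the longissimus CoG at an unadjusted two-sided 0.05. The plan has up to eight muscle-by-measure outcomes, reserves none, and invokes a multiplicity correction that the sizing ignores.

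If the correction is a Bonferroni split over four to eight tests, t-test power for the sized difference falls to about 60% to 50% at 21 per group, and 70% to 60% at a full 25. Even a split over two tests stays below 80% at 25 (78.7%). Holm over four CoG tests gives about 62–70% at 21. Under one joint test the power, and even the direction of the change, cannot be determined from the document.

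These figures assume a difference of 0.6, an SD of 0.68, a two-sided test and one number per CoG.

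**What to change.** In 2.5 and 2.6, name the one baseline longissimus CoG contrast on which the sizing rests. The authors should say which spinal level and which CoG measure it is, since 2.5 gives neither. Test that contrast at the full two-sided 0.05 and apply the multiplicity correction only to the remaining muscle and area outcomes. If the correction is meant to cover all of them, name the procedure and restate the power under it in place of 0.80.

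In the limitations paragraph of the Discussion, say that the sample size calculation covers only that single unadjusted cross-sectional contrast and does not by itself support sufficient power for the longitudinal comparison.

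The cost is a change of wording in three places, with no further enrolment. The downside is that the stated power becomes less favourable for every outcome other than the reserved contrast.
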